### **16.2 Data Entry**

Data entry system reflecting the CRFs will be prepared prior to study data entry stage.

Independent persons will enter data into the database system using double data entry techniques. Data identified as erroneous, or key data that are missing, will be referred to the CRA or, if necessary, to the Investigator for resolution on data query forms. On return of these forms, the database will be amended. Prior to the closure of the database, a quality control check of the raw data will be performed. All errors detected during the audit will be corrected prior to database closure.

### **16.3 Medical Information Coding**

Coding of AEs will be performed automatically by Medistat, using the Medical Dictionary for Drug Regulatory Activities (MedDRA) dictionary, using the most updated version. PT (preferred term) and SOC (System Organ Class) will be used.

The AE as well as SAE codes will be approved by the Sponsor.

Similarly, coding of all medications will occur using the WHO (World Health Organization) Drug dictionary. SAEs will be coded using MedDRA.

### **16.4 Data Validation**

Visual and computerized methods of data validation will be applied in order to ensure accurate, consistent, and reliable data for the subsequent statistical analysis. These procedures aim to detect out-of-range values, contradictory data, and abnormal evolutions over time, and possible undetected protocol violations (eligibility criteria, time and medication compliance, etc.).

#### **16.4.1 Data Correction**

After the data have been entered and verified, various edit checks will be performed for the purpose of ensuring the accuracy, integrity, and validity of the database. These edit checks may include:

- Missing value checks
- Range checks
- Consistency checks
- Sequence checks
- Probabilistic checks
- Protocol adherence checks

#### **16.4.2 Data Queries**

Data identified as erroneous, or key data that are missing, will be referred to the CRA or, if necessary, to the Investigator for resolution on data query forms for prompt resolution.

Queries will be generated after the second data entry is completed. Queries in a PDF format will be emailed to the sites. The emails will copy the CRA.

The resolved queries with the investigator's signature will be faxed to MediStat. The original documents will be mailed later.

On return of these forms, the database will be amended. All data modifications resulting from review or querying of the data will be electronically tracked.

Any errors detected by either the study monitor or the Investigator after query, resolution should be documented in CRF data change forms.

All the queries will be attached to the CRFs.

In all cases the signature of an investigator or designee and of the study Monitor will be required.

Prior to the closure of the database, a quality control check of the raw data will be performed. All errors detected during the audit will be corrected prior to database closure

#### **16.4.3 Data Extract**

All database tables are kept as raw data in SAS format. Each table (file) contains all the visits of the corresponding form.

#### **16.4.4 Source Documents**

Prescription forms, label logs and laboratory test results, and all other source documents should be maintained and kept at the study site in the patient study binder.

#### **16.4.5 Additional Documents and Records**

- 1) Patient screening log and patient assignment log – A listing of all patients who were screened, and those who have signed the informed consent form, respectively.

- 2) Patient identification log - This allows linking of the enrolled patient medical records to the study documents. Information should include, but is not limited to: patient's ID number, patient's name, date of birth, contact information, patient's non-identifiable study code. This list will be maintained by the investigational site.

## **17. QUALITY ASSURANCE AUDITS**

### **17.1 Good Clinical Practice**

The study described in this protocol will be carried out according to the local regulatory requirements (Israeli ministry of health) and FDA, ICH accepted standards of Good Clinical Practice. All procedures described in this protocol will be performed according to approved written Standard Operating Procedures unless otherwise stated.

### **17.2 Quality Laboratory Standards**

Bacteriologies laboratory tests/evaluations described in this protocol will be conducted in the hospital laboratories, accordance with quality laboratory standards as requested by the laboratory quality plan.

### **17.3 Quality Assurance Program**

There is no sponsor-audit planned in this study.

### **17.4 Regulatory Inspections**

The study may be inspected by regulatory agencies. These inspections may take place at any time during or after the study and are based on national regulations, as well as ICH guidelines.

## **18. STUDY MONITORING**

### **18.1 Monitors/CRA's and Monitoring Visits**

The study monitor/CRA will be responsible for ensuring adherence to Israeli Ministry of Health Regulations, ICH guidelines and the ENOX Standard operating procedures. Study Monitors for this trial will be provided by the Sponsor. The monitors will follow the current "Guideline for the Monitoring of Clinical Investigator" supplied by the FDA or will operate according to the EU Directives and in compliance with ICH guidelines.

Experienced independent monitors or monitors from CROs will also be trained in Physio-Logic Ltd SOPs, study protocol and the study monitoring conventions.

Regular monitoring of study data at the site will be performed as defined by the study specific monitoring plan. The site will be monitored to verify that enrolment rate, data recording, and protocol adherence are satisfactory. The frequency of monitoring may fluctuate depending upon enrolment rate, quantity of data collected and the complexity of the study, and will be described in the monitoring plan.

These monitoring visits will be performed for the purpose of verifying adherence to the protocol and the completeness and accuracy of data entered on CRFs. The study monitor will verify CRF entries by comparing them with the primary source documents (hospital/clinic/office records), which will be made available for this purpose. The monitor will review the maintenance of regulatory documentation. The Monitor will review the progress of the study with the investigator and other site personnel on a regular basis. Case report form sections may be collected during these visits. At the end of the study, a close-out monitoring visit will be performed. Monitoring visits will be arranged in advance with site personnel at a mutually acceptable time. Sufficient time must be allowed by the site personnel for the monitor to review CRFs and relevant source documents. The coordinator and/or investigator should be available to answer questions and provide clarifications, as needed.

### **18.2 Primary Source Documents**

The investigator must maintain primary source documents to support CRF data entries. These documents, which are considered "source data", may include but are not limited to:

- Demographic information
- Evidence supporting the diagnosis/condition for which the patient is being studied
- General information supporting the patient's participation in the study

- Medical history and physical findings
- Hospitalization or emergency room records (if applicable)
- Each study visit by date, including dates of catheter placement and removal, any relevant findings/notes by the investigator(s), and occurrence (or lack) of adverse events.
- Any additional visits during the study
- Any relevant telephone conversations with the patient regarding the study or possible adverse events
- Original, signed informed consent forms for study participation

The investigator must also retain all patient specific printouts/reports of tests/procedures performed as a requirement of the study. During monitoring visits the monitor will need to verify data in the CRFs against these source data.

## **19. USE OF INFORMATION AND PUBLICATION**

### **Confidential Information**

All information supplied by ENOX in connection with this study and not previously published, is considered confidential information. This information includes, but is not limited to, the investigators' brochure, clinical protocol, case report forms and other scientific data. Any data collected during the study are also considered confidential. This confidential information shall remain the sole property of ENOX, shall not be disclosed to others without a written consent of ENOX, and shall not be used except in the performance of this study.

The information developed during the conduct of this clinical study is also considered confidential, and will be used by ENOX in connection with the development of the medical device. The information may be disclosed as deemed necessary by ENOX. To allow the use of the information derived from this clinical study, the investigator is obliged to provide ENOX with complete test results and all data developed in this study. The information obtained during this study may be made available to other investigators who are conducting similar studies.

Should the investigator wish to publish the results of this study, the investigator agrees to provide ENOX with a manuscript for review 60 (sixty) days prior to submission for publication.

ENOX retains the right to delete from the manuscript information that is confidential and proprietary and to object to suggested publication and/or its timing (at the company's sole discretion).

In the event that ENOX chooses to publish the data from this study, a copy will be provided to the investigator at least 30 days prior to the expected date of submission to the intended publisher.

## **20. STUDY PERSONNEL**

### **20.1 Investigative Site**

#### **The Principal Investigator**

The principal investigator will have overall responsibility to lead the site study team and all aspects of the study in Beilinson. The Principal Investigator will oversee the accrual of appropriate patients, the conduct of the study according to the trial protocol, and the collection of required data.

#### **Study Coordinator**

A study coordinator or other staff member may be designated by the principal investigator to be responsible for patient scheduling and completion of all patients' case report forms and recording of adverse events. He/she will forward blood samples and requests to the appropriate laboratories, will obtain and forward laboratory results, and perform other duties delegated by the principal investigator as instructed.

### **20.2 Data Management and BioStatistics**

Medistat is responsible for adequate performance of the data management application using SAS; the conduct of the routine data management procedures; and the performance of the statistical analysis as defined in this protocol.

### **20.3 Monitor/Clinical Research Associate**

The Monitor/Clinical Research Associate (CRA) is responsible for monitoring the conduct of the study at the study centers. Monitoring visits will be arranged in advance, at a mutually acceptable time, with site personnel.

Monitoring is done by Enox personnel

The Medical Monitor is responsible for periodically reviewing all safety clinical data.

## **22. APPENDICES**

### **Appendix 1**

**Microscopic Examinations:**

Upon removal, the indwelling urinary catheter will be cut into 1-cm sections and the balloon section. Samples for EM will be cut into two transverse sections. One section of the urinary catheter is collected into an individual 50ml vial. Each vial is labeled by study coordinator: No., Group No., patient No., date of removal & collection time.

Immediately following collection, all the vials are stored at 2-8°C until their transportation to microbiology lab for bacteriological analysis.

The other section of the indwelling urinary catheter is collected into an individual 50ml vial, containing fixative (supplied by sponsor) for EM.

Each vial is labeled by study coordinator: Group No., patient No., date of removal & collection time.

Immediately following collection, all the vials are stored at 2-8°C and transported to the microbiology laboratory. In case transportation is delayed the vials can be stored overnight at 2-8°C and transported the next day for microbial and biofilm analysis.

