### 5.2 Observational

- Proportion of patients (%) who prematurely discontinued the study for any reason
- Measure and compare the biofilm formation on the surface of NO-impregnated versus non-impregnated Foley catheters after indwelling for 7-21±7 days
- Measure and compare bacteriuria (by urine culture) for NO-impregnated versus non-impregnated Foley catheters prior to insertion, on catheter insertion day, every day during hospitalization, on catheter removal day, and 30-45 days after catheterization
- Compare occurrences of clinically significant UTIs following catheterization with NO-impregnated and non-impregnated Foley catheters
- Record different species of bacterial contaminations

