## 6. STUDY DESIGN

### 6.1 Overview and Plan

This is a Prospective, Phase I, Open-label Case Series, Single-Center study.

A total of 12 patients, over the age of 18, undergoing radical prostatectomy will be enrolled. Screening data will be reviewed to determine patients' eligibility and informed consents will be obtained.

Patients who meet all inclusion criteria and none of the exclusion criteria will be enrolled.

6 patients will be allocated to receive NO-impregnated Foley catheters (treatment) followed by 6 patients allocated to receive non-NO-impregnated Foley catheters (control).

A patient will receive catheter up to  $21 \pm 7$  days of study treatment. A patient is considered as completed the study "per protocol", once study treatment was completed: 30-45 days after catheterization.

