### **Quantification of biofilm and Biofilm-forming bacteria:**

Quantitative measurement of bacterial biofilm and biofilm-forming bacteria will be determined by two methods: absorbance at 595nm using a spectrophotometer, and CFU measurement following sonication.

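### Catheter vials carry the group number, patient number and removal date, so the laboratory can know the arm when it makes the CFU and EM readings

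*Protocol*

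**What the plan says.** - **Labels.** Protocol Appendix 1 has two labelling instructions. For the bacteriology vial: "Each vial is labeled by study coordinator: No., Group No., patient No., date of removal & collection time". For the EM vial, which contains fixative: "Each vial is labeled by study coordinator: Group No., patient No., date of removal & collection time".
- **Destination.** Of the EM vials Appendix 1 says: "all the vials are stored at 2-8°C and transported to the microbiology laboratory". The bacteriology vials go to the microbiology laboratory as well.
- **Readings.** Section 11.3.2 quantifies biofilm by two methods: "absorbance at 595nm using a spectrophotometer, and CFU measurement following sonication". It also describes a roll plate of the exterior surface. Appendix 1 adds EM.
- **Use of the readings.** An observational endpoint in Section 5.2 is to "Measure and compare the biofilm formation on the surface of NO-impregnated versus non-impregnated Foley catheters after indwelling for 7-21±7 days". Section 13 tests the between-group difference with a two-sample t-test or a rank-sum test, two-tailed at 5%.
- **Masking and allocation.** Section 6.1 states: "This is a Prospective, Phase I, Open-label Case Series, Single-Center study". Allocation is sequential: "6 patients will be allocated to receive NO-impregnated Foley catheters (treatment) followed by 6 patients allocated to receive non-NO-impregnated Foley catheters (control". Randomization is marked not applicable in Sections 8.2 and 13.2. No section masks the laboratory, codes the specimens or names a masked reader.

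**The concern.** Open label explains why the surgeon, patient and clinical team know which catheter was used. It does not explain why the laboratory should. Nobody needs the arm in order to count colonies, read an absorbance or examine an EM section, yet the protocol instructs the coordinator to supply it.

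What is at stake is the comparison of biofilm between NO and control catheters. Some of these readings involve judgement, and a reader who expects less biofilm on NO catheters may lean that way without intending to. With six catheters per arm there is little averaging to absorb such a lean, and no analysis can remove it afterwards. The sponsor's account of its rabbit study in Section 3.1 shows how EM tends to be used: a visual impression of less biofilm on the impregnated catheters, with no count behind it.

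**Working it through.** The protocol states no figure on this point, so the check is mainly a comparison of its sections.

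**1. Does the label reveal the arm?** The protocol never defines the group number. The study has two groups, so it very probably means the arm; this is an inference.

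**2. Would deleting the group number be enough?** No. Twelve patients in two groups of six could be arranged in C(12,6) = 924 orders. Sequential allocation permits exactly 1 of them: six NO, then six control. Anyone who knows the design can read the arm from the patient number if numbers follow enrolment, and largely from the removal date.

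**3. Which readings can be influenced?**

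| Reading | Source | Scope for judgement | Between-arm analysis stated |
|---|---|---|---|
| EM | Appendix 1 | High: visual | No score or test defined |
| CFU after sonication | Section 11.3.2 | Partial: dilution and count | Yes, Section 13 |
| Absorbance at 595 nm | Section 11.3.2 | Little: instrument value | Yes, Section 13 |
| AEs and discontinuations (primary) | Section 5.1 | Not laboratory readings | Not affected by the vial label |

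**4. Could the planned tests respond to a bias?** With 6 versus 6 and no ties, the smallest two-sided exact rank-sum p-value is 2/924 = 0.0022, below 0.05. The tests can reach nominal significance even though Section 13.1 disclaims power.

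**5. Sensitivity, on assumed inputs only.** Suppose a continuous, roughly normal reading has no true difference between arms, and the reader shifts one arm by b standard deviations. The two-sample t-test has 6 + 6 − 2 = 10 degrees of freedom and noncentrality b/√(2/6) = b√3. Its two-sided 5% test then rejects with these probabilities:

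| Assumed shift b (SD) | False-positive rate |
|---|---|
| 0 | 5.0% |
| 0.25 | 6.8% |
| 0.5 | 12.3% |
| 0.75 | 21.8% |
| 1.0 | 34.7% |

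The protocol gives no value for b. The table shows how the test would react to a shift; it does not estimate one.

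**6. How far can masking go?** Section 11.3.2 requires the catheter to be cut within one hour of removal, and plates are incubated for 24 hours or overnight. Fresh specimens must be read as they come, in allocation order. EM sections are in fixative, so they are the ones that could be held and read together.

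**The case against.** The strongest case on the other side has five parts.

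- **The endpoints are observational and the study disclaims power.** True, and it limits the importance of the point. The protocol nevertheless plans the comparison and a 5% test for it.
- **The comparison is sequential and not randomized, so it is confounded with time anyway.** True. Masking does not cure that, but it removes a separate source of bias.
- **One of the two quantitative methods is an instrument reading.** True. Knowing the label can hardly move the spectrophotometer value.
- **Full masking is not achievable.** True for fresh specimens. Plates cannot be saved up and shuffled, and arrival date may hint at the arm to staff who know the design. A code also does not mask any choice of section made before the vial is labelled.
- **Laboratory procedures not shown may protect the reader.** Sections 17.1 and 17.2 refer to written procedures and a laboratory quality plan. These might hide the label from the EM reader, but nothing in the protocol says so, and Appendix 1 instructs the opposite.

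Two stronger readings are tempting and are not supported. A reader might infer that two borderline calls, one in each arm, would move the difference in proportion positive by 2/6 = 33 percentage points. The arithmetic is right, but the protocol defines no positive or negative call for biofilm or EM; Section 13 treats biofilm as a measured quantity, and its stated proportion concerns urinary tract infection. A reader might also extend the criticism to urine cultures. Appendix 1 does not describe urine labels, and those cultures serve eligibility and infection assessment, where prompt return to the right patient matters.

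**Conclusion.** The point stands as a modest one. The protocol instructs that catheter specimens reach the laboratory with three items that can each reveal the arm, and nothing in it masks the readers. EM is the most exposed reading, CFU counts are partly exposed, absorbance is little affected and the primary endpoints are untouched. No numerical size of the bias can be derived from the documents. The conclusion assumes that the group number means the arm and that the people making the readings see the label or the accompanying details. It does not imply that any reading would in fact be biased, or that masking could be complete or entirely without cost.

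**What to change.** Amend Appendix 1 before the first catheter is removed.

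1. Label each catheter vial, bacteriology and EM, with a random specimen code only. Take the group number, patient number, removal date and time off the label.
2. Keep the code list in the coordinator's log, with patient number, date and time. Traceability is preserved there.
3. Hold the fixed EM samples and read them as one batch in random code order. Appendix 1 provides only for overnight storage when transport is delayed, so its text must change, and the laboratory should confirm that the fixed material can be held.
4. Read the coded CFU plates as they arrive, and acknowledge in the report that their masking is partial.
5. Release the key after the laboratory data are locked.
6. Leave urine culture labels as they are for clinical use.

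The cost is new label text, a code list kept by the coordinator who already labels the vials, and a delay to the EM results while the batch is collected. No extra test or reader is needed.

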### 3. INTRODUCTION

#### 3.1 Background

According to recent publications by the World Health Organization (WHO) [1], hundreds of millions of patients are affected by health-care associated infections worldwide each year, resulting in prolonged hospital stays, long-term disabilities, deaths, and financial losses for health systems. The most common hospital-acquired infection is urinary tract infection (UTI), which accounts for almost 40% of all nosocomial infections [2]. According to the Center of Disease Control (CDC), most hospital-acquired UTIs are associated with catheterization [3]. In fact, urinary catheter-related bacteriuria is the most common health care associated infection worldwide [4]. Studies have showed that *Escherichia coli* is the most common bacterial pathogen responsible for catheter-associated UTIs (CAUTIs) [5, 6].

Planktonic bacteria can adhere to surfaces on catheters and colonize, creating a persistent environment called a biofilm [7, 8]. These colonies consist of bacteria that are highly differentiated and resistant to standard antibiotics [9], augmenting the potential of these pathogens to cause infections in patients with indwelling catheters.

In recent years, catheters coated with various antiseptic materials have been investigated for their ability to prevent biofilm formation and bacteriuria [10-13]. Several manufactures have marketed either antimicrobial-impregnated or silver-coated catheters as representing a technology to reduce CAUTI risk. More specifically, Nitric oxide (NO), an endogenously produced gas molecule, which plays an important role in host defense against various pathogens, has also been investigated for its potential to prevent biofilm formation [14, 15].

Using a novel approach, Regev-shoshani et al., generated antiseptic barrier on urinary catheters by impregnating them with NO [16]. Upon immersion in urine, these catheters demonstrated slow release of NO over a 14-day period and were able to prevent bacterial colonization and biofilm formation on their luminal and exterior surfaces [14]. In addition, they were also shown to inhibit the growth of *Escherichia coli* within the surrounding media and eradicated bacterial concentrations of up to  $10^4$  CFU/ml, suggesting the high potential of NO to prevent CAUTIs.

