### *In Vitro Studies*

In recent years, catheters coated with various antiseptic materials have been investigated for their ability to prevent biofilm formation on catheters, and bacteriuria [10-13]. More specifically, several techniques which involve the release of NO were developed and studied for their potential to prevent biofilm formation on catheters. For example, in an *in vitro* model of a catheterized urinary bladder, Carlsson et al. showed that a combination of nitrite and ascorbic acid, which releases low concentration of NO (maximum of 10ppm), effectively killed a clinical isolate of *Escherichia coli*, and a reference strain after 24 hour exposure [15].

Using a novel approach, in a study funded by ENOX, Regev-shoshani et al. [16] generated antiseptic barrier on urinary catheters by impregnating them with NO. These NO-impregnated catheters were then immersed in urine to simulate a clinically relevant static environment. According to results, slow release of NO from NO-impregnated catheters during a 14 days period prevent bacterial colonization and biofilm formation of *Escherichia coli* on their luminal and exterior surfaces. In addition, NO was able to eradicate up to  $10^4$  CFU/ml of bacteria within the surrounding media [14]. In another study, Regev-Shoshani et al. showed that NO-impregnated and antibiotic Nitrofurazone (NF)-coated catheters were equivalent in their antimicrobial activity and eradicated all bacteria in planktonic and biofilm states [16].

The mechanism by which NO prevents biofilm formation beyond simple eradication of the biofilm forming bacteria needs to be further clarified, yet it is speculated that NO prevents the attachment of bacteria and inhibition of biofilm formation in a mechanism which involves reduction and modification of proteins that mediate cell-substrate and cell-cell interactions [35-37].

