**Detection of bacteria on catheter**

Within removal of the catheter (1 hour maximum), cut the catheter into small 1-cm sections. 3 x 1-cm sections from each catheter will be analyzed per tests for biofilm formation as followed:

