#### CFU measurements:

A 1-cm section of the catheter is washed 3 times with saline. Transfer each section to 2 ml of saline 0.9% and sonicate for 20 seconds (30KHz). CFU's are determined by plating each sample on blood agar after serial dilution with saline and incubation at 37°C overnight.

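### Appendix 1 lets unfixed catheter sections wait overnight before culture, with no removal-to-plating limit; for NO catheters removed before day 14 this could lower CFU counts in that arm only

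*Protocol*

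**What the plan says.** Section 8.3.3 and the visit table in Section 6.2 send the removed catheter to Appendix 1 for processing. There the catheter is divided. For bacteriology, "One section of the urinary catheter is collected into an individual 50ml vial", with no medium, wash or neutralising agent named. The other section goes into a vial "containing fixative (supplied by sponsor) for EM". All vials are kept cold until transport, and the appendix adds: "In case transportation is delayed the vials can be stored overnight at 2-8°C and transported the next day for microbial and biofilm analysis".

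Section 11.3.2 describes the laboratory work. Its only time limit reads "Within removal of the catheter (1 hour maximum), cut the catheter into small 1-cm sections", and the paragraph on the exterior surface repeats it for the same step. The later steps carry no time limit: three saline washes, rolling on agar, sonication and plating, and crystal-violet staining.

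On the product, Section 3.1 reports that on immersion in urine "these catheters demonstrated slow release of NO over a 14-day period". The In Vitro Studies text says that "slow release of NO from NO-impregnated catheters during a 14 days period prevent bacterial colonization" of *E. coli* on both surfaces. Removal is at day 7-21±7 (Section 8.3.3).

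Biofilm on NO versus control catheters is an observational endpoint (Section 5.2). It is quantified by absorbance and by CFU after sonication (Section 11.3.2), and Section 13 tests it between groups at a two-sided 5% level.

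**The concern.** The comparison is meant to show how much viable biofilm formed on each catheter while it was in the patient. If a section from an NO catheter is still releasing NO when it goes into the vial, adherent bacteria can go on dying until someone washes and plates it. The control section carries no NO. The count would then mix what happened in the patient with what happened in the refrigerator, in one arm only.

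The design offers no protection. Allocation is six NO patients followed by six controls, without randomisation, so nothing balances transport delays between the groups. The vial label carries the removal date and collection time, but no plating time is required. As written, the delay could not be reconstructed at analysis.

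At stake is the CFU readout, the most direct measure of viable biofilm for a product whose rationale is preventing biofilm. A false signal here could steer later development.

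**Working it through.** **1. Does the overnight permission cover the culture sections?** The sentence follows the paragraph on the fixed vial, so it could be read as meant for electron microscopy alone. But it names microbial and biofilm analysis as the purpose, and the sentence before it refers to all vials. A fixed section cannot be cultured, so the permission reaches the unfixed section.

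**2. Does Section 11.3.2 exclude it?** The hour governs cutting. A site can cut within the hour, refrigerate overnight, and wash and plate next day without breaching either text. If the hour was meant as the limit for processing, Appendix 1 contradicts it. Either way the two places need aligning.

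**3. How much documented release is left at removal?** Release left = max(0, 14 − days in place).

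| Days in place | Release left (days) |
|---|---|
| 7 | 14 − 7 = 7 |
| 14 | 0 |
| 21 | 0 |
| 28 (21 + 7) | 0 |

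Insertion is study day 1, so counting by study day moves each cut-off by one day. The mechanism has documentary support only for catheters removed before about day 14.

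**4. Which measures are exposed?** Roll-plate and sonication counts need living bacteria and are exposed. Crystal violet measures dye bound to the surface, not viability, so it is less exposed. Fixed sections are not exposed.

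**5. What could it do to the planned test?** The protocol gives no figure to reproduce: no SD, no storage loss, no frequency of delay. As an illustration only, the exact Wilcoxon-Mann-Whitney test (6 versus 6, two-sided 0.05) was simulated 20,000 times per setting. Assumptions: one normally distributed log10 CFU value per patient, no true difference at removal, and a further loss of k log10 in a share s of NO sections. A section counts in s only if it was both held overnight and still active. Mean bias = k × s; for example 1 × 1/3 = 0.33 log10. False-positive rate, about 4% with no artefact:

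| SD (log10) | Share affected | k = 0.5 | k = 1 | k = 2 |
|---|---|---|---|---|
| 1 | all | 10.5% | 30.0% | 82.8% |
| 1 | half | 5.3% | 9.3% | 20.4% |
| 1 | one third | 4.7% | 6.4% | 10.6% |
| 2 | all | 5.6% | 10.6% | 30.3% |
| 2 | half | 4.3% | 5.2% | 9.4% |
| 2 | one third | 4.2% | 4.5% | 6.2% |

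If no section is held overnight, or every NO catheter comes out on day 14 or later, then s = 0 on the documents' evidence and there is no NO-specific bias.

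**The case against.** The overnight hold is an exception for delayed transport, it applies to both arms, and it may never be used. Release was shown in urine in vitro, and nothing describes release or killing on a used section in a cold vial. The endpoint is observational, and Section 13.1 disclaims power and significance. Sequential open-label groups could not carry a causal claim in any case. All of this stands. It limits the size and severity of the point but does not remove the gap in the handling rule.

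The documents do not support several stronger readings that a reader might infer:

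- **Every NO catheter is still active at removal.** The 14 days run from immersion, which means mostly or wholly while the catheter is in the patient.
- **The reported eradication of up to 10^4 CFU/ml bounds the loss.** That figure is for bacteria in the medium around immersed catheters, not adherent bacteria in a vial. The 2 ml of saline enters only at sonication, after storage and washing, so multiplying by it describes nothing that happens during the hold.
- **The bias always favours the product.** That direction holds for NO carry-over in CFU counts. Ordinary storage changes can occur in either arm.
- **The whole biofilm comparison is compromised.** Only the culture counts are materially exposed.

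It can also be said that same-day plating shortens carry-over without abolishing it, and that dropping values thins a small comparison. Both are true. The first is still a gain, and the second is a cost to accept knowingly.

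**Conclusion.** The point holds in a limited form and at low severity. The protocol permits unfixed sections to wait overnight before culture and sets no removal-to-plating limit. Its own description of the product makes killing after removal plausible in the NO arm, for catheters removed before about day 14. The possible effect is a lowering of NO-arm roll-plate and sonication counts by an amount the documents cannot supply.

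The simulated rates show only that the result depends on three unknowns: the loss per section, the share of sections affected, and the spread of counts. Across the settings shown, the false-positive rate runs from close to its nominal value to far above it. The conclusion assumes that the in vitro release carries over at least in part to a refrigerated section. If it does not, the missing time limit remains an inconsistency to tidy, but there is no arm-specific bias. Safety and tolerability conclusions do not depend on this point.

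**What to change.** Put one handling rule in Section 11.3.2 and Appendix 1, the same for both arms:

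- Wash and plate the roll-plate and sonication sections on the day of removal, within a stated maximum time from removal agreed with the site microbiologist.
- Record plating time next to the removal date and collection time already on the label.
- Restrict overnight storage to the electron-microscopy and crystal-violet sections.
- List any CFU result from an overnight-held section but leave it out of the between-group CFU comparison. At the least, prespecify a sensitivity analysis without it.

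The cost is a few lines of wording and one time field. Removal visits must fit the laboratory's receiving hours, and an occasional CFU value will be lost from a 6 versus 6 comparison. Because the arms are enrolled in sequence, losses may fall unevenly, so the number of held sections should be reported by group.
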